### Study design and procedure

The study is designed as a multi-center, randomized controlled trial (RCT). Data will be collected in 14 Dutch and Belgian mental healthcare institutions. Within each institution, TAY meeting the inclusion/exclusion criteria, their parents/caregivers and their therapists will be asked to participate in the study. Parents/caregivers of adolescents younger than 16 will be directly involved in the study. TAY aged 16 and older will be asked first for permission to contact their parents/caregivers. If they agree, their parents/caregivers will be asked to participate in the study as well. Before enrolling in the study, written informed consent from TAY and parents/caregivers/legal representatives (for adolescents younger than 16) will be obtained. If parents/caregivers and therapists agree to participate, they will be asked for their own written informed consent as well.

In total, six multiple informant (TAY, parents/caregivers, therapist) assessments will be conducted: at baseline (T0), after 3 sessions (T1), after 6 sessions (T2), after 9 sessions (T3), at post-intervention (T4) and at 6-month follow-up (T5). Assessments will include diagnostic interviews (at T0, T4 and T5) and questionnaires (at T0 to T5). The assessments will be conducted by research assistants working at the participating institutions (e.g., master students and psychologists). Research assistants will be trained in administering the diagnostic interview and questionnaires. The TAY will receive a 30 euro gift card as a reward (5 euros per assessment). After the baseline assessment (T0), TAY will be randomly assigned to either the ACT your way or TAU condition using a computer generated block design. At each institution, five participants will be randomly allocated to the ACT your way condition and five participants will be randomly allocated to the TAU condition (blocksize = 10). See Fig. 1 for an overview of the study design.

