#### Sample size calculation

We calculated the sample size for a two-level multilevel analysis, using the Optimal Design program [64]. In accordance with our planned analyses, the first level represents the TAY and the second level represents the therapists. As most of the therapists either give the ACT your way or the TAU intervention, we calculated the sample size as for a cluster RCT in which the therapists represent the clusters. Within our sample size calculation, we used a cluster size (i.e., the expected number of therapists) of 70, as we expect that in both conditions approximately 35 therapists will be carrying out either the ACT your way or TAU intervention. In addition, we used an ICC of 0.05 as this is the average ICC reported in meta-analyses of therapist effects in psychological intervention research [65]. Furthermore, the effect size is based on a meta-analysis in which 39 RCT’s were included that investigated the efficacy of ACT, including 1,821 adults with various mental disorders [21]. We based the effect-size on this meta-analysis as, to our knowledge, this is the most recent meta-analysis examining the effects of ACT transdiagnostically. When ACT was compared to TAU a medium effect was found (Hedges g = 0.64), when ACT was compared to CBT a small effect was found (Hedges g = 0.32). In this study ACT will be compared to TAU, presuming a medium effect around 0.64. However, since we want to be conservative and expect that, at least with some of the participants, CBT will be used in TAU as well, an effect size of 0.50 was included in the sample size calculation. Hence, with a cluster size of 70, an effect size of 0.50, an ICC of 0.05, an α of 0.05 and a power of 0.8, a sample size of 140 (i.e., on average two TAY per therapist, and 70 TAY per condition) is assumed.

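### A fixed block of 10 equal to each institution's 5:5 quota makes the tenth allocation, and on average one in six, certain in advance at every institution that fills its block

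*Protocol article*

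**What the plan says.** The section on study design and procedure gives the scheme in full. Timing: "After the baseline assessment (T0), TAY will be randomly assigned to either the ACT your way or TAU condition". Method: "using a computer generated block design". Control arm quota and block size: "five participants will be randomly allocated to the TAU condition (blocksize = 10". The experimental arm has the matching quota: "At each institution, five participants will be randomly allocated to the ACT your way condition". The same section sets the number of sites: "Data will be collected in 14 Dutch and Belgian mental healthcare institutions". The sample size section gives the total: "a sample size of 140 (i.e., on average two TAY per therapist, and 70 TAY per condition) is assumed".

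Three other statements bear on who can see the sequence. Eligible youth and their therapists are approached within each institution. The assessments are done by research assistants who work there. In the sample size section, "most of the therapists either give the ACT your way or the TAU intervention". The article does not state masking status, who holds the allocation list, or who in the institution makes the approach.

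**The concern.** When the block size is fixed and known, and equals the number each institution is to enrol, the end of the sequence can be deduced from its beginning. Once one arm has its five places, every remaining allocation at that institution is determined. A person who knows the count and decides whom to approach, or when, could match patients to the known arm.

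Randomising after T0 does not prevent this, because a determined allocation is known before the next person is approached. Concealing the list centrally does not prevent it either, because the deduction needs only the quota and the allocations already seen.

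The eligibility criteria are broad, which leaves room for discretion. One primary outcome is self-reported and the other comes from an interview by local research assistants. If participants were selected by arm on unmeasured prognosis, adjustment for measured baseline variables would not reliably remove the bias.

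**Working it through.** **Inputs.** Block of 10 with 5 per arm; 14 institutions; N = 140 (study design and sample size sections). For power: "with a cluster size of 70, an effect size of 0.50, an ICC of 0.05, an α of 0.05 and a power of 0.8". Two-sided testing is assumed, because the article does not state sidedness.

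**1. The plan's own figures.**
- 14 × 10 = 140, so the total corresponds to one block per institution.
- With 70 therapists and 2 participants each, SE = √[4 × (0.05 + 0.95/2)/70] = √0.03 = 0.173.
- The non-centrality is 0.50/0.173 = 2.89. On 68 degrees of freedom the power is 0.812, so the stated sample size reproduces.

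**2. Certain allocations in a fixed block of 10.** There are C(10,5) = 252 equally likely sequences. An allocation is certain if one arm's five places are already used.

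| Certain at the end of the block | Sequences | Share |
|---|---|---|
| 1 | 140 | 55.6% |
| 2 | 70 | 27.8% |
| 3 | 30 | 11.9% |
| 4 | 10 | 4.0% |
| 5 | 2 | 0.8% |

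- Mean: (140×1 + 70×2 + 30×3 + 10×4 + 2×5)/252 = 420/252 = 1.67 per block. For a block of 2m the closed form is 2m/(m+1) = 10/6.
- Share: 1/6 = 16.7%. Over 14 institutions: 14 × 1.67 = 23.3 of 140.
- At least two certain: 112/252 = 44.4%. At least three: 42/252 = 16.7%.
- By position: none in 1 to 5; then 0.8%, 4.8%, 16.7%, 44.4% and 100% for positions 6 to 10.
- Always guessing the arm with more places left is right 65.3% of the time.

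**3. If the block is not filled.** Summing the position probabilities up to the stopping point:
- stop at 9: 0.667/9 = 7.4%;
- stop at 8: 0.222/8 = 2.8%;
- stop at 5 or fewer: 0.

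**4. Is 10 the wrong size?** The certain share of a known fixed block is 1/(m+1): 50% for size 2, 33% for 4, 25% for 6, 20% for 8 and 16.7% for 10. Ten is the best of these.

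**5. Varying blocks of 6, 8 or 10, equally likely, with no 5:5 stop.** Assume the worst case, in which the observer knows the set of sizes but not the size in use. Over the first ten participants, certainty requires a block of 10 (probability 1/3), one arm used up, and a history that rules out a completed block of 6 or 8.
- Positions 6, 7 and 8: one third of the fixed-block values, that is 0.0026, 0.0159 and 0.0556.
- Positions 9 and 10: the first six must not be 3:3 and the first eight must not be 4:4. Within a block of 10 this has probability 1 − (0.476 + 0.556 − 0.317) = 0.286, so 0.286/3 = 0.095 for each position.
- Sum: 0.26 per ten, against 1.67. Best-guess accuracy is 64.4%.
- Sizes 4, 6 and 8 give 0.24 per ten and 65.9% accuracy.

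**6. Precision cost of step 5.** After ten participants the split is 5:5 at 70.2% of institutions, 6:4 at 29.0% and 7:3 at 0.9%. Relative information is n₁n₂/25: 1, 0.96 and 0.84. The mean is 0.702 + 0.278 + 0.007 = 0.987. Non-centrality becomes 2.89 × √0.987 = 2.87, and power goes from 0.812 to about 0.807.

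**The case against.** The strongest reply is that the exposure is assumed. About 70 therapists share 140 participants, which is about five therapists per institution with two participants each, so one therapist sees only part of the local sequence. The article does not say that enrolling staff keep a count or were told the block size. This stands. The figures apply to someone who has followed the whole sequence. With ten participants per site that is easy, but it is an inference.

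It can also be said that recruitment may fall short, since the discussion section itself calls it a possible challenge. This stands too: one in six requires filled blocks, and the share drops quickly below ten.

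Third, the analysis controls for the baseline level of each outcome and adds baseline variables that differ between arms. These safeguards are partial, because they cannot reach unmeasured reasons for approaching one person and not another.

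Fourth, equal arms at each site have a purpose, given institution dummies and possible group delivery. That is a real but small cost.

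A reader might go further and infer that selection took place, that allocation is unconcealed, or that a block of 10 is too large. The documents support none of these. They report no enrolment. An article may leave concealment to the full protocol. Among fixed blocks up to 10, size 10 has the lowest certain share.

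**Conclusion.** The point holds as a weakness in a stated design choice. The cause is a fixed block size, printed in the article, that coincides with the site quota. If every institution fills its ten places, about 23 of 140 allocations (17%) can be deduced in advance by anyone who has followed the sequence, and the tenth can be deduced everywhere.

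This rests on two assumptions that the article does not state: that blocks fill as planned, and that someone involved in enrolment knows the earlier allocations. The second is plausible because therapists and participants necessarily know the treatment and the institution recruits, treats and assesses. No bias in the treatment effect has been estimated, and none can be from the documents.

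**What to change.** For allocations still to be made, keep stratification by institution. Replace the fixed block with randomly varying block sizes, for example 6, 8 and 10, that are not disclosed to the sites. Remove the exact 5:5 stop per institution.

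This changes the randomisation settings only. Certain allocations fall from 1.67 to about 0.26 per ten, or from about 23 to about 4 of 140 (14 × 0.26 = 3.7). Ordinary guessing remains about as successful as before.

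The price is a 6:4 split at roughly three institutions in ten, occasionally 7:3, power of about 0.807 instead of 0.812, and less even numbers for group delivery.

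A big-stick rule with a maximum imbalance of 3 is not the better answer to this point. It lowers best-guess accuracy to 56%, but still leaves about 1.22 certain allocations per ten, and these can occur from the fourth participant on.

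If recruitment is already complete, report the scheme as a limitation and compare the baseline characteristics of late-block participants by arm. With about 23 such allocations expected, that comparison can show only gross differences.

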**Fig. 1 Fig1:**
[figure not shown]
Overview of study design. *****Only if TAU is carried out weekly. If TAU is carried out bi-weekly, the T1, T2, T3 and T4 take place after 2, 4, 6 and 8 sessions, respectively

### Study conditions

#### ACT your way

ACT your way consists of 12 weekly sessions, that can be carried out both individually as in groups. The therapists at the clinical institutions decide if they carry out ACT your way individually or in a group. There is a guide for therapists [66], a workbook for TAY [67] and a website with additional videos, mindfulness exercises and information for TAY. Each session lasts either 120 (group therapy) or 60 (individual therapy) minutes and has a fixed format in which psychoeducation, mindfulness exercises, metaphors and experiential exercises are carried out. The 12 sessions are divided into four blocks, each comprising of three sessions. The first block focusses on values (i.e., desires regarding development, identity, and autonomy). The second block focusses on the six core processes of psychological inflexibility (i.e., experiential avoidance, cognitive fusion, dominance of conceptualized past and feared future, attached to the conceptualised self, lack of values, and inaction). The third block focuses on acquiring skills based on the six core processes of psychological flexibility (i.e., acceptance, cognitive defusion, contact with the present moment, self as context, values, and committed action). With these skills, TAY can consciously choose behaviours that fit their chosen values. The fourth block focusses on continuing and strengthening TAY’s psychological flexibility and preparing the TAY for possible relapses in the future. In this study, ACT your way will be carried out in a face-to-face format by therapists working at the participating mental healthcare institutions. The therapists will be trained in using ACT your way (i.e., a two day training in the basics of ACT and a two day training in ACT your way specifically). Moreover, during the course of the study, the therapists will be supervised by an ACT expert.

#### Treatment as usual

TAU can also be carried out both individually as in groups and will consist of a broad range of different psychological interventions, such as CBT, parent counselling, emotion regulation training, running therapy, or psychodynamic therapy. Therapists of the participating mental health care institutions decide what intervention(s) are most suitable to be carried out as TAU. We expect that in most cases, similar to ACT your way, TAU will also consist of weekly sessions. However, in the few cases that this is not possible, it is also acceptable to have bi-weekly sessions within TAU. If TAU is carried out bi-weekly, the T1, T2, T3 and T4 will take place after 2, 4, 6 and 8 sessions, respectively. We choose this option as then both in the ACT your way as TAU condition, the assessments will take place approximately around the same time.

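### The session numbers set for bi-weekly TAU put its assessments progressively later than the ACT assessments, by 3 to 4 weeks at T4, although they were chosen to coincide

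*Protocol article*

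**What the plan says.** The ACT your way section states: "ACT your way consists of 12 weekly sessions, that can be carried out both individually as in groups". Under Study design and procedure, T1, T2 and T3 follow 3, 6 and 9 sessions, T4 is the post-intervention visit and T5 the 6-month follow-up. For ACT, T4 therefore comes after session 12.

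The Treatment as usual section expects weekly sessions in most cases but adds that "in the few cases that this is not possible, it is also acceptable to have bi-weekly sessions within TAU". For those participants: "If TAU is carried out bi-weekly, the T1, T2, T3 and T4 will take place after 2, 4, 6 and 8 sessions, respectively". The purpose is stated directly afterwards: with these numbers, "the assessments will take place approximately around the same time" in both conditions. The Fig. 1 legend repeats the rule ("If TAU is carried out bi-weekly, the T1, T2, T3 and T4 take place after 2, 4, 6 and 8 sessions, respectively"), so it is not an isolated slip.

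The Effectiveness section compares the conditions at T4 and T5 as nominal visits, each adjusted for the baseline level of the outcome. Both primary outcomes are measured at these two visits.

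**The concern.** The bi-weekly numbers have one purpose: to make the visits coincide in calendar time. Going from weekly to two-weekly sessions should halve the session count at each visit, but the plan cuts it only by a third (12 to 8, 9 to 6, 6 to 4, 3 to 2). The visits must then drift apart as treatment goes on, with the largest gap at T4, where the primary outcomes are compared.

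Only TAU may be bi-weekly, so the drift is in one arm and one direction. Affected TAU participants have more elapsed time, and with it more natural course and possibly more treatment, before T4. Their T2 and T3 mediator measures are also taken later than in the ACT arm.

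**Working it through.** **Inputs.** ACT interval 1 week, visits after sessions 3, 6, 9 and 12 (ACT your way; Study design and procedure). Bi-weekly TAU interval 2 weeks, visits after sessions 2, 4, 6 and 8 (Treatment as usual; Fig. 1 legend). I assume that sessions run without gaps and that the first session falls equally soon after randomisation in both arms.

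**Formulas.** The week of session *k* at interval *i* can be counted in two ways:
- A, first session at week 0: (k − 1) × i
- B, each session closes its interval: k × i

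**The plan's own claim.** The stated aim implies a gap of about 0 weeks at every visit.

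| Visit | Sessions ACT / TAU | A: ACT / TAU week | Gap A | B: ACT / TAU week | Gap B |
|---|---|---|---|---|---|
| T1 | 3 / 2 | 2 / 2 | 0 | 3 / 4 | 1 |
| T2 | 6 / 4 | 5 / 6 | 1 | 6 / 8 | 2 |
| T3 | 9 / 6 | 8 / 10 | 2 | 9 / 12 | 3 |
| T4 | 12 / 8 | 11 / 14 | 3 | 12 / 16 | 4 |

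The claim is reproduced only at T1, and exactly only under A. The gap then grows by one week per visit. At T4 the delay is 3/11 = 27% (A) or 4/12 = 33% (B).

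**Other reading of bi-weekly.** If it meant twice a week, 8 sessions would take 8/2 = 4 weeks against 12. That does not match either.

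**T5.** If six months (26 weeks) run from T4, T5 falls at 14 + 26 = 40 against 11 + 26 = 37 weeks (A), or 16 + 26 = 42 against 12 + 26 = 38 weeks (B). The gap is again 3 or 4 weeks.

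**Effect on the arm mean.** Mean TAU delay at T4 = bi-weekly share × gap. The article gives no share, so these are assumptions:
- 5% (3.5 of 70): 0.05 × 3 = 0.15 to 0.05 × 4 = 0.2 weeks
- 10% (7 of 70): 0.3 to 0.4 weeks
- 20% (14 of 70): 0.6 to 0.8 weeks

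**Which session numbers would coincide.** Under B, 3 bi-weekly sessions end at week 6 (T2) and 6 end at week 12 (T4). T1 (week 3) falls between sessions 1 and 2, and T3 (week 9) between sessions 4 and 5. Under A, T1 matches session 2 and T3 matches session 5, while T2 and T4 lie one week from sessions 3 or 4 and from 6 or 7. Under neither count does 8 match T4.

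**The case against.** The strongest reply is that this hardly matters: the text claims only approximate agreement, T1 agrees to within a week, few participants are concerned, and T4 is meant as a post-intervention visit, for which anchoring to sessions is a legitimate choice. The small average effect stands. But the gap is systematic rather than scatter around zero, and if session anchoring is the real intention, the reason printed for these numbers is not the true one.

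The Discussion also provides for adding treatment duration as a covariate if it differs between arms. That is relevant but does not align the visits: it concerns length of treatment rather than time from baseline to assessment, and it is measured after randomisation.

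A reader might infer more than the article supports:
- *The whole TAU arm is assessed 3 to 4 weeks late.* Only the bi-weekly participants are. A share as high as half of TAU would contradict the expectation of few cases.
- *T5 is certainly shifted.* The aims in the introduction contrast an effect immediately after the intervention with one after six months, which points to T4 as origin, but no origin is stated and the figure is not shown. Counted from baseline, T5 would not move.
- *Participants who stop early have no due date.* The Discussion says they will still be asked for both later assessments. Exact dates are operational detail that an article leaves to the full protocol.
- *The economic results are distorted.* The Cost-effectiveness section sets a 6-month period, and nothing shown establishes how a later T4 would enter it.
- *The shift favours ACT.* If participants tend to improve with time, a later TAU assessment favours TAU and would slightly dilute a true ACT advantage.

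**Conclusion.** The point holds as an internal contradiction: the session numbers under Treatment as usual and in the Fig. 1 legend miss the aim stated for them, under either way of counting weeks. For a bi-weekly TAU participant the delay at T4 is 3 weeks (27%) or 4 weeks (33%). For the TAU arm as a whole it is about 0.15 to 0.8 weeks if 5% to 20% are treated bi-weekly, an assumed range. A delay at T5 depends on the further assumption that follow-up is timed from T4. The effect on the treatment contrast is likely to be small, but it runs in one direction, falls at a primary analysis point and can be avoided cheaply. It should be corrected; it does not put the design in doubt.

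**What to change.** Re-set the bi-weekly TAU assessment points so that T1 to T4 fall at the calendar times of the weekly schedule. Counted to interval end, these are weeks 3, 6, 9 and 12: T2 after 3 bi-weekly sessions, T4 after 6, and T1 and T3 at the matching week, since no session ends exactly there. Time T5 from that same nominal T4 in both arms and say so. Correct the Treatment as usual section and the Fig. 1 legend together.

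No new recording is needed to describe exposure in TAU: under Other characteristics, therapists already report at T1 to T4 how many sessions took place since the previous assessment.

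The work is two text corrections and new due dates in the assessment monitoring system. The real cost is that bi-weekly TAU participants will have had fewer sessions at T4 (about 6 or 7 rather than 8), and some may still be in treatment, so for them T4 is no longer strictly post-intervention. This should be stated when results are reported. No change to treatment frequency is proposed, and moving every visit in both arms to fixed calendar windows is not required to resolve this point.

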### Measures

See Table 1 for an overview of all measures used in the study.

**Table 1 Tab1:** Overview of study measures

Variable	Domain	Instrument	Items	Source			Assessment					
				**Y**	**P**	**T**	**T0**	**T1**	**T2**	**T3**	**T4**	**T5**
Primary outcomes	Psychological flexibility	AFQ-Y (FV)	17	x			x		x		x	x
		AFQ-Y (SV)	8	x				x		x		
	Number of DSM-5 diagnoses	SCID-5 Junior	-	x			x				x	x
Secondary outcomes	Presence of the primary DSM-5 diagnosis	SCID-5 Junior	-	x			x				x	x
	Psychopathology	YSR	69	x			x				x	x
		CBCL	74		x		x				x	x
		BFS	12	x			x	x	x	x	x	x
	Personality problems	SIPP-SF	60	x			x		x		x	x
	Global Functioning	CGAS	1			x	x		x		x	
		ORS	4	x			x	x	x	x	x	x
	Individual and societal functioning	ISIQ	10	x			x				x	x
	Quality of life	EuroQol	6	x	x		x		x		x	x
	Stress	PSS (FV)	10	x			x		x		x	x
		PSS (SV)	5	x				x		x		
	Treatment satisfaction	SSS	4	x							x	
	Drop-out	Drop-out questionnaire	5			x					x	
	Therapeutic alliance	TASC	12	x		x		x	x	x	x	
Moderators	Demographic characteristics	-	-	x	x	x	x				x	x
	Type of problems	SCID-5 junior	-	x			x				x	x
	Severity of problems	SCID-5 junior	-	x			x				x	x
	Psychopathology of parents/caregivers	ASR	69		x		x				x	x
	Treatment expectancy	PETS	7	x			x					
	Previous treatments	VEHI	8	x			x					
Mediators	Psychological flexibility	AFQ-Y (FV)	17	x			x		x		x	x
		AFQ-Y (SV)	8	x				x		x		
	Emotion regulation	ERSQ	27	x			x		x		x	x
		ERSQ (SV)	9	x				x		x		
		FEEL-KJ	30	x			x		x		x	x
	Self-compassion	SCS-SF	12	x			x		x		x	x
	Autonomy	AAQ	18	x			x		x		x	x
	Perfectionism	FMPS	26	x			x		x		x	x
	Self-esteem	RSES	10	x			x		x		x	x
	Group cohesion	GCQ-S	12					x	x	x	x	
Other characteristics	Treatment integrity	Observation	-									
	Content of TAU	TPC	3			x		x	x	x	x	
	Life events	LES	23	x			x				x	x
	Costs	Cost diary	79	x			x				x	x

Abbreviations: *FV* Full-length version, *P* Parents/caregivers, *SV* Short version, *T* Therapist, *T0* Baseline assessment, *T1–3* mediator assessments, *T4* Post-assessment, *T5* 6-month follow-up assessment, *Y* Transitional age youths

